### Population

Inclusion criteria are consecutive, consenting adult outpatients (> 18 years) with IPF (group 1), NSIP (group 2) and COPD (group 3) already diagnosed prior to the consultation (index) date. Probable and definitive IPF diagnosis will be made according to the Fleischner Society Consensus [42], NSIP diagnosis with the American Thoracic Society classification [2, 43], and COPD with the Global Initiative for Chronic Obstructive Lung Disease criteria [44]. Consenting, age-matched (± 2.5 years) individuals with normal lung function (spirometry, lung volume and transfer factor for carbon monoxide [TL_CO_]) followed in the outpatient clinic with a similar quality of electronic medical records, but for diseases other than the outcome of interest, will serve as the 1:1 control group (group 4). This latter group will comprise patients with obstructive sleep apnoea, follow-up of occupational lung diseases (miners, chemical workers, etc.), and follow-up of pulmonary nodules (considered benign after 2 years). Reasons for pulmonary follow-up among the controls will be reviewed and reported in a supplementary file. Identifying all cases with the outcome of interest and selecting controls for comparison is a more efficient and resource-sparing study design than a full cohort study. Exclusion criteria are: (1) patients who cannot be mobilised for posterior auscultation; (2) those known for severe cardiovascular disease with pulmonary repercussions; (3) patients known for a concurrent, acute, infectious pulmonary disease (e.g., pneumonia, bronchitis); (4) patients known for asthma exclusive from COPD; (5) patients with alpha-1-antitrypsin deficit; (6) a physical inability to follow procedures; and 7) inability to give informed consent.

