### Study procedure

The study will be performed over a period of 6 months. Recruitment can be stopped before the anticipated end if the inclusion of 160 patients is reached before. A trained research nurse/doctor ([name]) will recruit the subjects during a single routine consultation in the outpatient clinic. This will include checking the selection criteria for each patient prior to study participation, obtaining written informed consent, administering questionnaires on demographic characteristics (age, sex, occupation, long-term exposure to occupational or environmental agents, etc.), relevant medical history, and symptomatic presentation (Additional file 1), which will be captured by an electronic case report form to be completed by the study coordinator on a tablet. The nurse/doctor will also administer the standardised K-BILD [47], CAT [48], and SF-36 [49] severity assessment questionnaires, and record lung sounds during 5–7 min with an electronic stethoscope in the same zones as LUS acquisition, as previously proposed by our group [40]. For the LUS examination using a standard point-of-care ultrasound device, an adapted version of our previous 10-point acquisition protocol [50] will be used, which involves scanning the anterior superior, anterior inferior, posterior superior, posterior inferior and lateral thorax regions. In addition, pulmonary functional tests (conducted with patients in a stable condition) will be collected, as well as chest X-rays with two incidences (posterior-anterior and lateral) and HRCT scans for IIP patients (within 12 months). Controls will not be exposed to a chest X-ray and/or CT scan unless required as part of their routine follow-up; cases will have undergone such imaging given that it is part of their diagnostic evaluation.

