### Sample size calculation

Each patient will provide 10 audio recordings of 30 s. Samples will be considered at the patient level with all 10 recordings. In deep learning, sample size calculation is an intractable problem that is usually discovered through empirical investigation. The number of samples required to reach a certain performance criterion is dependent on the characteristics of the dataset, the diversity and number of the classes, the degree of data augmentation possible, as well as the complexity of the learning algorithm. Thus, sample size calculations cannot rely on the traditional statistical heuristics that are often used in biostatistics. Rather, sample size estimations in deep learning are mostly made by analogy. Evaluating existing knowledge on similar datasets, we find that the expected proportion of velcro-like crackles in IIP patients is nearly 100% [4], whereas the prevalence of coarse crackles is 71% in COPD patients [58]. The exclusivity of these sounds among groups is not known, but overlap is assumed to be minimal and pathological sounds are by definition absent in non-ILD and non-COPD control subjects. Assuming a similar discriminative power compared to a previous work done by our group (personal communication) to distinguish between normal and pathological lung sounds in pneumonia from 80 patients in balanced classes (40 pathological; 40 controls) with 8 auscultation sites of 30 secs each, we estimate using the same number of patients in each class to achieve convergence at above 80% of the area under the receiver operating characteristic curve (AUROC). Thus, we will aim to enrol at least as many patients in each group: 80 ILD (40 IPF, 40 NSIP); 40 COPD; and 40 controls (i.e., known not to have ILD or COPD, and with normal lung function). As the recruitment site would expect 120 ILD patients (40% with IPF; 60% with NSIP) and 100 with COPD over the space of one year, this number is achievable in the time frame of the study (6 months), even with a 70% consent rate.

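### The stated caseload does not support 40 IPF, 40 NSIP and 40 COPD patients in 6 months at 70% consent, and IPF falls short even if the whole year's pool is approached

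*Protocol article*

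**What the plan says.** The section on sample size in the protocol article sets the targets as "80 ILD (40 IPF, 40 NSIP); 40 COPD; and 40 controls" and treats them as minima: "we will aim to enrol at least as many patients in each group". The figure of 40 per class comes by analogy from the group's earlier work on pneumonia sounds, with 40 pathological and 40 control patients. It is the stated ground for expecting an AUROC above 80%.

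The section closes with feasibility. The site expects "120 ILD patients (40% with IPF; 60% with NSIP) and 100 with COPD over the space of one year", and from this it concludes that "this number is achievable in the time frame of the study (6 months), even with a 70% consent rate". The study procedure section gives the same period: "The study will be performed over a period of 6 months". It allows recruitment to end early once 160 patients are in, and mentions no extension. The population section says that cases are "already diagnosed prior to the consultation (index) date".

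**The concern.** The sentence sets an annual caseload against a half-year window and a 70% consent rate, and claims targets that those inputs do not produce. Half of 48 IPF patients is already below 40 before consent is considered.

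At stake is the group size on which the plan leans. The AUROC expectation rests on a 40-versus-40 precedent, and IPF versus NSIP is one of the listed tasks under the primary outcome. If the IPF group ends at about 17, five-fold cross-validation leaves about 3 IPF patients per test fold (17/5 = 3.4) instead of 8 (40/5). That task then lies well outside the precedent used to size it.

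**Working it through.** **Inputs** (all from the sample size section; the 6 months also appears under study procedure):
- ILD caseload 120 a year, of which IPF 120 × 0.40 = 48 and NSIP 120 × 0.60 = 72
- COPD caseload 100 a year
- window 6 of 12 months; consent 70%
- target 40 in each group

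**Attempt to reproduce the plan's figure.** Expected enrolment = annual caseload × share of the annual pool seen × consent rate. Under even accrual the share is 6/12 = 0.5.

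| Group | 6 months, 70% consent | 6 months, 100% consent | Whole annual pool, 70% consent | Target |
|---|---|---|---|---|
| IPF | 48 × 0.5 × 0.7 = 16.8 | 24 | 33.6 | 40 |
| NSIP | 72 × 0.5 × 0.7 = 25.2 | 36 | 50.4 | 40 |
| COPD | 100 × 0.5 × 0.7 = 35.0 | 50 | 70.0 | 40 |
| All cases | 77.0 | 110 | 154.0 | 120 |

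None of these variants gives 40 in all three groups. In the first column the groups stand at 42%, 63% and 88% of target.

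**Consent needed for 40 in 6 months, even accrual:** 40/24 = 167% for IPF, 40/36 = 111% for NSIP, 40/50 = 80% for COPD. The first two are impossible.

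**Share of the annual pool that must attend within 6 months at 70% consent:** 40/33.6 = 119% for IPF (impossible), 40/50.4 = 79% for NSIP, 40/70 = 57% for COPD.

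**Months to 40 at 70% consent, even accrual:** 12 × 40/33.6 = 14.3 for IPF, 12 × 40/50.4 = 9.5 for NSIP, 12 × 40/70 = 6.9 for COPD.

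**Pooled ILD, 6 months, 70% consent, even accrual:** 16.8 + 25.2 = 42. This is below the target of 80 but not below the 40 per class of the precedent.

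**Precision for IPF versus NSIP.** The true AUROC of 0.80 is an assumption, taken at the plan's own threshold. The Hanley–McNeil variance is

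[A(1 − A) + (n₁ − 1)(Q₁ − A²) + (n₂ − 1)(Q₂ − A²)]/(n₁n₂),

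with Q₁ = A/(2 − A) = 0.6667, Q₂ = 2A²/(1 + A) = 0.7111 and A² = 0.64.
- 40 v 40: (0.16 + 39 × 0.02667 + 39 × 0.07111)/1600 = 0.00248; SE 0.0498; 95% half-width 0.098.
- n₁ = 17, n₂ = 25: (0.16 + 16 × 0.02667 + 24 × 0.07111)/425 = 0.00540; SE 0.0735; half-width 0.144.
- n₁ = 25, n₂ = 17: (0.16 + 24 × 0.02667 + 16 × 0.07111)/425 = 0.00456; SE 0.0675; half-width 0.132.

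The half-width therefore grows from about 0.10 to between 0.13 and 0.14, depending on which class is treated as positive.

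**The case against.** The strongest reply is that halving the annual figure assumes patients arrive evenly and once each. The study enrols people who already have their diagnosis, at routine visits, and the article does not say whether 120 and 100 count new cases or people under follow-up. If they are a follow-up pool, more than half may attend within 6 months. At 70% consent the whole ILD pool gives 120 × 0.7 = 84 against 80, and the COPD pool gives 70 against 40. The sentence would then hold for ILD and COPD as totals, provided about 95% of the ILD pool (80/84) attended in the window.

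This stands in part. A reader might infer that no disease group can reach 40. That is true only under even accrual, since NSIP and COPD could get there with faster attendance. But the article states no such pattern, and the reply does not help IPF: the 84 splits into about 34 IPF and 50 NSIP, not 40 and 40. If the caseload counts only new diagnoses and existing patients come on top, the pool would be larger, but no figure for that is given.

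A reader might also infer that the expectation of an AUROC above 80% falls altogether. The documents do not support that either. The lead tasks pool IPF and NSIP, and about 42 pooled ILD patients still meet the 40-per-class precedent on the ILD side.

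It is also fair that the article calls the study a pilot of modest size, words the target as an aim, and sizes by analogy rather than by a power calculation. A recruitment shortfall is visible as it happens and does not in itself bias an estimate.

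**Conclusion.** The feasibility statement is wrong as written. For IPF this needs no accrual assumption: at 70% consent the stated caseload gives at most 33.6 patients, even if a full year's pool is approached within 6 months. For NSIP and COPD it depends on how fast the pool attends. Under even accrual, the natural reading of an annual figure set against a half-year window, they reach about 25 and 35. They reach 40 only if about 79% and 57% of their annual pools attend in the window.

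The main consequence is for IPF versus NSIP, where the 40-per-class basis is not met. Under even accrual the 95% half-width at a true AUROC of 0.80 is about 0.13 to 0.14 instead of 0.10. Also under even accrual, COPD is slightly short for ILD versus COPD (about 42 v 35). ILD versus controls keeps its basis on the ILD side; the control yield is not stated and cannot be checked.

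Two things remain unknown: what the caseload counts, and whether it is already net of the exclusion criteria. If it is not, the yields would be lower.

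**What to change.** State whether the annual caseload counts new cases or patients in follow-up, and whether it is before or after the eligibility criteria. Then reconcile the sample size and study procedure sections in one of two ways:

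1. Lengthen the stated recruitment period. If accrual is even, IPF at 70% consent sets it at about 14 to 15 months. If the caseload is a fixed follow-up pool, that figure does not apply, because later months would bring back people already approached, and the authors would need to derive their own.
2. Keep 6 months, restate the expected groups (about 17 IPF, 25 NSIP and 35 COPD under even accrual; at most about 34 IPF), and withdraw the claim that 40 per group is achievable in that time.

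Under the second option, also state that the 40-per-class basis for an AUROC above 80% is not met for IPF versus NSIP and, under even accrual, is slightly short for COPD, while pooled ILD still meets it on the ILD side of the comparison with controls.

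The cost is wording and a less favourable timeline or group-size figure. No study procedure changes.

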### Statistical analysis plan

For descriptive statistics related to the clinical data collected, all continuous variables will be reported as medians with their interquartile ranges. Binary and categorical variables distribution will be reported as proportions and percentages. To evaluate baseline demographic differences and outcomes differences between the case and control patients, conditional logistic regressions will be used to account for the matched design. Pearson’s and Spearman’s correlation coefficients will be used to assess the relationship between continuous variables normally and non-normally distributed, respectively. For the primary outcome, each task will be quantified using descriptive statistics (i.e., proportion and type of abnormalities), as well as the AUROC, sensitivity, specificity, positive predictive value, negative predictive value, and likelihood ratios (with 95% CIs over a fivefold cross-validation).

The diagnostic accuracy of each echographic sign will be assessed and sensitivity, specificity, positive predictive value, negative predictive value, positive likelihood ratio, and negative likelihood ratio with their 95% CIs will be calculated. To find the combination of echographic signs with the best diagnostic accuracy, we will compare the performance of several multivariable models, such as logistic regression, random forest and neural networks. Performance will be reported on a test set comprising 20% of the data in a tenfold cross-validation with 95% CIs. As a secondary objective, we will aim to compare the predictive performance of human expert-identified acoustic signatures in the above predictive tasks. First, we will describe the expert labels by the percentage of sound labels attributed to each diagnosis. A multivariable logistic regression will be derived using the clinical data and sound labels to estimate the diagnoses, as for the primary objective. A kappa score will be used to assess the concordance between *DeepBreath* and expert diagnosis consolidated into a basic predictive model.

The K-BILD, CAT and SF-36 questionnaires will be analysed with descriptive statistics. Associations between the questionnaires’ sum scores and lung function parameters will be quantified by Spearman’s rank correlation coefficient. We will consider correlations < 0.3 as negligible, ≥ 0.3 to < 0.5 as low, ≥ 0.5 to 0.7 as moderate, and ≥ 0.7 as strong.

Missing data will be reported and padded with zero in the deep learning network and also assessed according to other labels. Features with more than 50% missing values or with a significant bias in missing data fields will be removed and reported. All statistical tests will be two-sided with a type-I error risk of 5%. Data analysis will be carried out using the latest version of R (R Foundation, Vienna, Austria) for descriptive statistics and statistical tests.

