## Background

Interstitial lung disease (ILD) encompasses several pulmonary conditions defined by an alteration of the pulmonary interstitium, a restrictive pattern of lung function, and fibrotic scarring on chest computed tomography (CT). Approximately one-third of these disorders have known endogenous or exogenous causes, including environmental or occupational factors, infections, drugs and radiation. Two-thirds are of idiopathic aetiology [1] and comprise a range of subcategories, the most common of which is idiopathic interstitial pneumonia (IIP). In turn, IIP comprises a range of sub-pathologies, such as idiopathic pulmonary fibrosis (IPF) and non-specific interstitial pneumonia (NSIP) [2]. Identifying patients with IIP at the earliest possible stage is essential for care management as treatment is aimed at slowing the irreversibly debilitating and ultimately fatal progression. Delay in specialist referral is associated with a higher mortality, irrespective of disease severity [3]. With a mean delay of 2.2 years between the onset of symptoms and specialist referral, the investigation of competing diagnoses by non-specialist providers can be costly for both patients and healthcare providers [3]. However, given the initial non-specific symptomatic presentation, the need for advanced diagnostic tools, such as high-resolution chest CT (HRCT), and an expertise in the early-stage diagnosis of IPF and NSIP remain desirable and achievable objectives [4]. Distinguishing between IPF and NSIP raises considerable diagnostic challenges as their clinical presentations share many overlapping features. However, the distinction is useful as their response to treatment differs markedly [5]. Until now, with limited treatment options benefiting mostly patients in the early stages of the disease [6, 7], many patients will progress towards disability or death [8]. Despite research and advances in therapy, ILDs remain a worldwide health challenge affecting millions of people each year [9], emphasizing the need to make progress in diagnosis and prevention.

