### Primary and secondary outcomes

The primary outcome is the diagnostic of ILD, both IPF and NSIP, versus control subjects or COPD. We will assess the predictive performance of the *DeepBreath* algorithm-evaluated lung auscultation and LUS in the following identification and risk stratification tasks as follows: (1) to discriminate ILD from control subjects (according to expert clinical diagnosis [42]); (2) to differentiate ILD from COPD; (3) to predict ILD clinical severity (according to a HRCT grading scale^1^ and lung function tests^2^); and (4) to differentiate the subcategories of ILD (such as IPF, NSIP) according to the gold standard diagnosis [2, 43, 44]).

Secondary outcomes are the clinical, functional and radiological characteristics of IPF, NSIP and COPD diagnosis. We will: (1) compare the predictive performance of human, expert-identified acoustic and LUS signatures in the above predictive tasks (Kappa coefficient); (2) assess diagnostic performance of a model trained to detect crackles; (3) explore the utility of adding clinical data (signs, symptoms, demographics, medical history and basic paraclinical tests) to the breath sound algorithms; and (4) determine the impact of the diseases on subjects’ health-related quality of life measured with the standardised King’s Brief Interstitial Lung Disease (K-BILD) [47], the COPD assessment test (CAT) [48], and the 36-item Medical Outcomes Study Short-Form Health Survey (SF-36) [49] severity assessment questionnaires.

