## Pulmonary function tests and chest CT scan

For all subjects, spirometry, body-plethysmographic parameters (see details above) and lung diffusion capacity for carbon monoxide (TLco/Kco) will be measured. Participants’ lung images recorded from previous HRCT (or X-rays) during past routine visits will be used. No chest CT scans will be performed as part of this study; only lung images of participants previously recorded as part of their regular follow-up or to be performed in this context will be used. The presence on the chest CT scan of honeycombing, traction bronchiectasis, reticulations, ground-glass opacities, and emphysema will be measured for patients with IPF, NSIP or emphysema. The main chest CT scan features of IPF are reported to be basal and peripheral reticulations, traction bronchiectasis, minimal ground glass opacities, and moderate or extensive honeycombing. For NSIP, the CT scan typically demonstrates bilateral lung involvement and invariably some extent of ground-glass opacities, mainly in the lower zones with fibrotic changes, while honeycombing is not a common feature [55]. The presence on the chest CT scan of structural abnormality, such as ≥ 5% emphysema and/or ≥ 15% gas-trapping and/or airway wall thickness ≥ 2.5 mm [56], will be measured for patients with COPD. The protocol assumes normal lung parenchyma in the control group, which will not be exposed to radiation unless controls have already undergone a recent (i.e., < 5 years) chest CT scan for other reasons. This will be taken into consideration as we will investigate the association of lung sounds with radiological characteristics.

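### Case-control regressions would test variables that control selection already fixed, and the logistic model on sound labels is separated if the sample-size premise holds

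*Protocol article*

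**What the plan says.** All references are to the protocol article.

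- **Model for group comparisons** (Statistical analysis plan): to evaluate demographic and "outcomes differences between the case and control patients, conditional logistic regressions will be used to account for the matched design". The outcomes meant are not listed there.
- **What counts as an outcome** (Primary and secondary outcomes): "Secondary outcomes are the clinical, functional and radiological characteristics of IPF, NSIP and COPD diagnosis".
- **Who can be a control** (Population): "individuals with normal lung function (spirometry, lung volume and transfer factor for carbon monoxide" also normal.
- **Control imaging** (Pulmonary function tests and chest CT scan): "The protocol assumes normal lung parenchyma in the control group". Controls are not imaged for the study.
- **Lung function in ILD** (Background): the disease group is described as including "a restrictive pattern of lung function". The eligibility criteria for IPF and NSIP give no numerical lung-function limit.
- **Crackle premise** (Sample size calculation): velcro-like crackles are expected in nearly all IIP patients and coarse crackles in 71% of COPD patients, while "pathological sounds are by definition absent in non-ILD and non-COPD control subjects".
- **Model on expert labels** (Statistical analysis plan): "A multivariable logistic regression will be derived using the clinical data and sound labels to estimate the diagnoses". It is followed by a kappa between DeepBreath and the expert labels combined into a simple predictive model.

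**The concern.** There are two separate problems.

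**Selection on the tested variable.** Once diagnosis (assessed by AUROC and related measures) and the questionnaires (descriptive) are set aside, the outcomes left for the conditional regressions are chiefly the clinical, functional and radiological characteristics. Controls were chosen because their lung function is normal, and their parenchyma is taken to be normal. A small p-value for a case-control difference in these variables would look like a finding, but it could not be told apart from the enrolment rule.

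**Separation in the label model.** If controls have no crackles, a logistic regression of diagnosis on a crackle label has an empty cell. The maximum likelihood estimate of that coefficient does not exist, and adding clinical covariates does not bring it back. Software typically prints a very large coefficient with a huge standard error and a Wald p-value near 1 for what may be the strongest sign in the data. An unpenalised fit of this kind also tends to give overconfident predictions.

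**Working it through.** The plan has no figure of its own to reproduce for these regressions. The 40 per group was set by analogy with unpublished work (40 + 40 + 40 + 40 = 160, which adds up).

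**Inputs from the article:** 80 ILD (40 IPF, 40 NSIP), 40 COPD, 40 controls; 1:1 age matching; crackles nearly 100% in IIP, 71% in COPD, 0 in controls; two-sided 5% tests.

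**Assumptions:** 40 matched pairs, because 1:1 matching with 120 cases and 40 controls leaves the matched sets undefined; crackle rate in ILD *p* = 0.95 to 1.00; crackle rate in controls *q* = 0 to 0.10; the lung-function distributions given below.

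**1. Lung function as normal/abnormal.** In 1:1 conditional logistic regression the odds ratio is *b/c*, where *b* counts pairs with only the case abnormal and *c* pairs with only the control abnormal. Eligibility forces *c* = 0, so the estimate is infinite whenever *b* > 0. With *b* = 28 (an illustrative count), Newton iterations give log odds ratios of 6.2, 11.2 and 21.2 at steps 5, 10 and 20, with Wald p-values of 0.14, 0.83 and 0.998. The exact McNemar p-value is 2 × 0.5^28 = 7.5 × 10⁻⁹.

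**2. Selection alone, continuous lung function.** Cases and potential controls were drawn from the same distribution (SD 15), and controls were kept only at 80% predicted or above. A paired t-test on 40 pairs served as a proxy for the conditional model.

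| Source mean | Rejection at nominal 5% |
|---|---|
| 100 | 13% |
| 90 | 57% |
| 85 | 87% |

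**3. Is continuous lung function separated?** Controls were given mean 100 and SD 12, truncated at 80. The probability that all 40 pairs are ordered the same way is:

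- FVC with case mean 85 to 75 (SD 15): about 0.00 to 0.04
- TLCO with case mean 50 (SD 15) to 40 (SD 12): 0.92 to 1.00

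So FVC can overlap and a markedly reduced TLCO would not. In both cases step 2 still applies.

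**4. Label model, ILD versus control, 80 v 40, unmatched.** A zero cell arises if no control has crackles or if every ILD patient does:

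P(zero cell) = 1 − (1 − (1 − *q*)^40)(1 − *p*^80)

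- *q* = 0: 1.00 for any *p*. With *p* = 0.98, 0.98^80 = 0.20, so separation is complete on crackles alone in about 20% of samples and quasi-complete in the rest.
- *q* = 0.05, *p* = 0.98: 1 − (1 − 0.129)(1 − 0.199) = 0.30
- *q* = 0.05, *p* = 0.95: 0.14
- *q* = 0.10, *p* = 0.98: 0.21

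**5. COPD versus control, 40 v 40, *p* = 0.71.** P(zero cell) is 1.00 at *q* = 0, 0.13 at *q* = 0.05 and 0.015 at *q* = 0.10. This contrast is not among the listed diagnostic tasks, so it matters only if the label model is fitted for it.

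**6. Does penalisation help prediction?** In a simulation of 80 v 40 with assumed clinical covariates, ridge raised out-of-sample accuracy from about 0.96–0.97 to 0.98–0.99 and at least halved the log-loss. The covariates are assumed, so this is indicative only.

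**The case against.** The strongest reply has five parts.

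- **The conditional models name no variable.** This is true. Lung function and imaging follow from reading the outcomes section together with the analysis section. A reader might go further and infer a planned case-control odds ratio for crackles, but the article does not support that: the secondary objective relates crackles to patient characteristics within IPF and NSIP (and similarly COPD).
- **Absence of crackles in controls is a planning premise, not an eligibility rule.** This stands. Experts label the recordings blinded, controls may include people followed for occupational lung disease, and the article says the exclusivity of these sounds between groups is unknown. Separation in the label model is therefore conditional on the premise.
- **A separated model still classifies.** This also stands. Fitted probabilities go to 1 or to a finite proportion, and the kappa can be computed. A reader might infer that the comparison with DeepBreath collapses, and that does not follow.
- **Exact inference remains possible.** For a single binary exposure this is correct: 28 of 28 discordant pairs gives a lower 95% limit of 7.1 for the odds ratio. The estimation method could also be in a fuller plan that is not shown. But no estimator removes selection on the outcome.
- **Lung function is not perfectly separated.** This is correct for continuous FVC. The defect there is selection, not a missing estimate.

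**Conclusion.** The concern holds in two limited forms.

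1. If lung function or imaging features enter the conditional regressions, which is the natural reading of the outcomes listed, the tests largely restate how controls were chosen. A normal/abnormal lung-function odds ratio is infinite by construction once a case is abnormal. Continuous measures may give finite estimates, but their p-values do not separate disease from selection. The 13% to 87% range rests on assumed distributions and on 40 pairs.
2. The logistic model on expert sound labels is completely or quasi-completely separated for ILD versus control if the article's crackle premise is exact. Its coefficients and Wald intervals are then unusable and its predictions are likely to be overfitted. The problem shrinks if some controls have crackles, to about 30% at 5% in controls with 98% assumed in ILD.

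The AUROC, sensitivity, specificity and related measures planned for DeepBreath do not depend on these regressions. Comparisons on variables that played no part in selecting the groups, such as sex, are also untouched.

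**What to change.** In the Statistical analysis plan section:

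- Restrict the case-control conditional regression to named variables that did not select or match the groups, for example sex and smoking status.
- Report lung function and CT features descriptively by group, without case-control p-values, and say that controls were enrolled with normal lung function.
- Fit the diagnosis model containing sound labels, and any logistic model containing LUS signs, by penalised likelihood: Firth, or ridge with the penalty tuned inside the training folds.

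The cost is a few sentences and standard R functions. Coefficients will be somewhat shrunk, and a few p-values will no longer be reported. No change to recruitment, data collection or the primary analysis is needed.
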